### **9.2.1. Handling missing data**

To minimise possible biases, participants will continue to be followed up even after protocol treatment violation. However, it is possible that there will still be some missing data at the end of the study so sensitivity analyses will be carried out to investigate the robustness of the results. Methods based around multiple imputation will be used. Further details will be given in the Statistical Analysis Plan.

### **9.2.2. Proposed frequency of analysis**

- Twice yearly review of recruitment and compliance for StAmP Trial Steering Committee.
- Quarterly interim analyses of adverse events for confidential review by the DMEC for safety.
- Twice yearly review of data quality for review by the DMEC
- Main analyses of efficacy of Pravastatin once all participants have reached 6 week follow up.

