## **2.5. Aims and objectives of this proof of principle trial**

The aim of the trial is to establish whether pravastatin will lead to a significant reduction of anti-angiogenic factors in women with early-onset pre-eclampsia. To test this hypothesis, we will ask the following questions:

1. Does pravastatin cause a greater inhibition of circulating anti-angiogenic factors in women with early-onset pre-eclampsia compared with placebo?
2. Are there any adverse or beneficial effects to the mother or the baby following gestational exposure to pravastatin?
3. If pravastatin appears to safely inhibit circulating anti-angiogenic factors, how best can a substantive trial/health technology assessment be undertaken to develop guidance for routine use of statins to prevent or ameliorate pre-eclampsia?

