## **7.2. Reporting AEs**

All adverse events, from the first administration of trial treatment until 6 weeks after child-birth, whether observed directly or reported by the patient, will be collected and recorded. Non-serious adverse reactions or events are not required to be reported in an expedited manner, but will be recorded on the daily data collection forms.

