**Birmingham Clinical Trials Unit:**

- To report SUSARs to MHRA and main REC within required timelines as detailed above
- To prepare annual safety reports to MHRA, main REC and TSC.
- To prepare SAE safety reports for the DMEC at 3-monthly intervals. Data will be presented blinded to treatment, but the DMEC will be able to review unblinded data if necessary.
- To report all fatal SAEs to the DMEC for continuous safety review
- To notify Investigators of SUSARs which compromise patient safety

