### 8.2. Secondary outcome measures

Secondary measures will be:

- The level of maternal circulating sFlt-1 and the ratio of sFlt-1 to PlGF over the first 14 days post-randomisation. Most women are expected to provide regular measurements before childbirth. Pregnancy with pre-eclampsia is expected to last for an average  $11\pm 5$  days, so estimates of effects over the first two weeks are expected to be from a largely complete set of data. All available data, both clinical and biochemical will be examined to see if this influences interpretation of results.
- Severity of pre-eclampsia as indicated by maternal blood pressure, level of proteinuria, platelet count, liver-transaminases, renal function, fetal biometry and umbilical artery blood flow 48 hours after randomisation and for the remainder of the pregnancy.
- Length of gestation post-randomisation, in days.
- Maternal morbidity, as indicated by serum creatinine  $\geq 120\mu\text{mol/L}$ , proteinuria  $\geq 5\text{g/24h}$ ; signs of left ventricular failure (pulmonary oedema, oxygen sats  $< 95\%$ ); hypertension  $\geq 170/110\text{mmHg}$  despite anti-hypertensive treatment; disseminated intravascular coagulation and/or platelets  $< 50 \times 10^9$ ; eclampsia; cerebrovascular event; liver transaminase  $\geq 500\text{IU/L}$ , more than 48 hours after randomisation and for the remainder of the pregnancy.
- Neonatal Apgar score at 1, 5, 10 minutes
- Use of anti-hypertensives
- Level of pravastatin in the cord blood at delivery relative to maternal levels.
- Serious adverse events and reactions

Secondary outcomes will be collected prior to randomisation, daily throughout pregnancy and at birth. The data items collected to identify secondary outcomes are shown in Table 1.

When analyzing secondary outcomes, length of gestation post randomization will be considered the most important indicator of potential clinical efficacy.

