| CTG                                                               | X                      | X                           |                |                            |                             |
| Liquor volume                                                     |                        | X                           |                |                            |                             |
| Umbilical artery Doppler                                          | X                      | x                           |                |                            |                             |
| Maternal serum and umbilical cord blood pravastatin concentration |                        |                             | X              |                            |                             |
| Gestational age                                                   |                        |                             | X              |                            |                             |
| Apgar score at 1,5,10 minutes                                     |                        |                             | X              |                            |                             |
| Congenital anomalies                                              |                        |                             | X              |                            | x                           |
| Neonatal mortality/ morbidity                                     |                        |                             | X              | X                          | X                           |
| Length of maternal and perinatal hospital stay and location       |                        |                             |                | X                          |                             |
| Serious adverse events or reactions                               | X                      | X                           | X              | X                          | X                           |

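### Symptomatic non-serious adverse events are recorded for every woman, but the protocol specifies no comparison of them between pravastatin and placebo

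*Combined protocol and SAP*

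**What the plan says.** **Collection.** Section 7.2 covers "All adverse events, from the first administration of trial treatment until 6 weeks after child-birth". Non-serious events are not expedited but "will be recorded on the daily data collection forms". Section 7.6 makes the local principal investigator responsible for recording all events, non-serious ones included.

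**Outcomes.** The one adverse-event item among the secondary outcomes in section 8.2 is "Serious adverse events and reactions". The matching row of Table 1 is "Serious adverse events or reactions".

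**Analysis.** Section 9.2 sets methods for sFlt-1, the sFlt-1/PlGF ratio, length of gestation, other continuous measures and dichotomous outcomes. It does not mention adverse events. Section 9.2.2 lists "Quarterly interim analyses of adverse events for confidential review by the DMEC for safety" and, at the end of the trial, "Main analyses of efficacy of Pravastatin once all participants have reached 6 week follow up".

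**Interim reporting.** Sections 7.3 and 7.6 describe the three-monthly report to the DMEC as a report of serious adverse events. Of that report, section 7.6 says: "Data will be presented blinded to treatment, but the DMEC will be able to review unblinded data if necessary". Under section 7.3 the Trial Steering Committee sees only blinded data.

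**Objective.** The second question in section 2.5 is "Are there any adverse or beneficial effects to the mother or the baby following gestational exposure to pravastatin".

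**The concern.** The trial asks an open question about harm, collects the data to answer it, and then names only the serious part as an outcome. A statistician working from sections 8.2 and 9.2 would tabulate serious events by arm and would have no instruction to do the same for the rest.

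Most of the pravastatin reactions in Appendix D (dizziness, headache, gastrointestinal symptoms, rash, fatigue, myalgia) would rarely meet the seriousness criteria in section 7.1. Section 7 itself warns that metabolic changes in pregnancy could alter the drug's toxicity in ways not foreseen. Section 2.6 also expects the trial to supply safety information for later trials.

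If the final report carried serious events only, a common but non-serious tolerability problem would sit in the database unreported, and readers could take the absence of a table as absence of an effect. The placebo comparison is what separates a drug effect from the symptoms of pre-eclampsia and its other treatments, so pooled or blinded counts would not answer the question.

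**Working it through.** The point rests mainly on what the sections specify, so they are set side by side first. The arithmetic then shows what a by-arm table could deliver.

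**1. Which harms already have a by-arm analysis?**

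| Type of harm | Listed as an outcome | Method in 9.2 |
|---|---|---|
| Serious events and reactions | 8.2, Table 1 | Dichotomous: risk ratio, chi-squared |
| Transaminases, renal function, platelets, blood pressure | 8.2, Table 1 | Continuous: baseline-adjusted |
| Maternal morbidity | 8.2, Table 1 | Dichotomous |
| Apgar score; congenital anomalies; neonatal mortality and morbidity | 8.2 and/or Table 1 | Continuous or dichotomous |
| Symptomatic non-serious events | Not listed | None stated |

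Only the last row is uncovered. Muscle effects fall there in particular: Appendix D flags myalgia, weakness and raised CK as of special interest, but Table 1 has no CK row, so only adverse-event recording would pick them up.

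**2. What does the quarterly report contain?** Section 9.2.2 says adverse events. Sections 7.3 and 7.6 say serious adverse events, blinded by default. Section 10.3 says safety and morbidity outcomes, plus anything else the committee requests. These do not settle whether non-serious events reach the DMEC at all.

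**3. What would a by-arm table show?**

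Inputs: up to 64 women (section 9.1), allocated equally (section 5.3), so at most 64/2 = 32 per arm. The event rates are assumptions, except the 1.4% for myalgia, which is in Appendix D.

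The plan's own totals of 34 (single time point) and 32 (repeated measures) reproduce with a t-test calculation, at 17 and 16 per arm. They concern sFlt-1 and do not bear on this point.

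Half-width of the 95% CI for a risk difference when both arms have rate p: 1.96 × √(2p(1−p)/n). For p = 0.10 and n = 32: 1.96 × √(0.18/32) = 1.96 × 0.075 = 0.147.

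| Assumed rate | 32 per arm | 16 per arm |
|---|---|---|
| 5% | ±11 points | ±15 points |
| 10% | ±15 points | ±21 points |
| 20% | ±20 points | ±28 points |
| 30% | ±22 points | ±32 points |

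The 16-per-arm column applies if only the required total of 32 were available.

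Chance of at least one case among 32 women on pravastatin, 1 − (1−p)^32:
- 1.4%: 0.36 (0.45 cases expected)
- 5%: 0.81 (1.6 expected)
- 10%: 0.97 (3.2 expected)

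No events in 32 women leaves a one-sided 95% upper bound of 1 − 0.05^(1/32) = 8.9%.

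Exact power of Fisher's two-sided 5% test at 32 per arm: 10% v 5%, 2%; 20% v 10%, 11%; 25% v 5%, 48%; 30% v 5%, 68%. Only very large differences are testable, which argues for estimates with intervals rather than tests.

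**The case against.** A reader might infer that serious events are the trial's only safety outcome and that non-serious toxicity will never be compared by arm. The documents do not support that.

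- **Other safety outcomes exist.** Sections 8.2 and 9.2 bring liver, renal, platelet, maternal-morbidity and neonatal measures into the randomised comparison without requiring an event to be serious. Section 7.1 counts complications of pre-eclampsia and laboratory deterioration as adverse events, so part of the non-serious spectrum is already covered. This stands and narrows the point to symptoms.
- **The blinding default is written for serious-event reports.** Extending it to the quarterly adverse-event analyses of section 9.2.2 is an inference. The DMEC may unblind or request other analyses, and section 10.3 withholds from it only unblinded results of the main outcome. This stands. Even so, confidential committee review does not produce a reported result.
- **Detail is deferred.** Section 9.2 promises a fuller statistical analysis plan, whose text is not in the documents. The supportable wording is therefore *not specified in the protocol*.
- **Section 9.2.2 is a timing list.** Read literally, its reference to efficacy would exclude serious events too, although they are a listed outcome. The word is loose and does not show that safety is excluded. The stronger evidence is the outcome list, which does stop at serious events.
- **The yield is small.** At the background rates in Appendix D little would be seen in either arm. This is true, and it is why the table should be descriptive.

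**Conclusion.** The point holds in a limited form. All adverse events are collected, the adverse-event outcome is restricted to serious ones, and the protocol specifies no by-arm analysis of symptomatic non-serious events, although the trial's second question is not restricted in that way. Laboratory measures, morbidity and neonatal outcomes are not affected.

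No result or sample size in the plan changes. What is at stake is the completeness of the answer on harm. At 32 per arm the table would exclude only large differences: about ±15 points at an assumed 10% rate, or an upper bound of 8.9% after no events in 32. These figures assume full recruitment to 64, complete recording and the rates shown. The separate analysis plan may already close the gap, but that cannot be seen from the documents.

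This is a cheap improvement that should be made. It does not threaten the primary analysis.

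**What to change.** 1. In section 8.2 and Table 1, keep the serious-event outcome as it is and add a further one: *all adverse events, serious and non-serious*. Adding rather than replacing keeps serious events separately listed.
2. In the last bullet of section 9.2.2, make the end-of-trial analysis one of *efficacy and safety*.
3. In section 9.2 or the statistical analysis plan, specify a table by randomised arm of the number and percentage of women with at least one event, overall and by body system, with muscle symptoms on their own line. Give risk differences with 95% confidence intervals and no significance tests. No separate liver line is needed, since transaminases are already an outcome.
4. Reconcile section 9.2.2 (adverse events) with sections 7.3 and 7.6 (serious adverse events, blinded by default) on what the quarterly DMEC report contains and how it is blinded.

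**Cost:** a few lines of wording and one or two tables, from data already collected. **Downside:** with so few women some chance differences will appear across body systems, so the table should be labelled descriptive and its width stated.

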## **10. DATA ACCESS AND QUALITY ASSURANCE**

### **10.1. In-house Data Quality Assurance**

The trial will adopt a centralised approach to monitoring data quality and compliance. A computer database will be constructed specifically for the trial data and will include range and logic checks to prevent erroneous data entry. Independent checking of data entry will be periodically undertaken on small sub-samples. The trial statistician will regularly check the balance of allocations by the stratification variables.

The StAmP Trial Co-ordinator will perform hospital site visits as part of the trial monitoring plan, as agreed and reviewed by the Trial Management Group, Trial Steering Committee and Data Monitoring and Ethics Committee. This will involve source data verification.

#### **10.1.1. Monitoring and Audit**

Investigators and their host Trusts will be required to permit trial-related monitoring and audits to take place by the StAmP Trial Coordinator, providing direct access to source data and documents as requested. Trusts may also be subject to inspection by the Medicines and Healthcare Products Regulatory Agency and/or by the Research and Development Manager of their own Trust and should do everything requested by the Chief Investigator in order to prepare and contribute to any inspection or audit. Trial participants will be made aware of the possibility of external audit of data they provide in the participant information sheet.

#### **10.1.2. Trial drug quality assurance**

To verify the integrity of the randomisation list and labelling process, a sample of capsules will be destruction tested from each batch of treatment packs produced.

### **10.2. Independent Trial Steering Committee (TSC)**

The TSC provides independent supervision for the trial, providing advice to the Chief and Co- Investigators and the Sponsor on all aspects of the trial and affording protection for patients by ensuring the trial is conducted according to the principles of Good Clinical Practice in Clinical Trials.

If the Chief and Co-Investigators are unable to resolve any concern satisfactorily, Principal Investigators, and all others associated with the trial, may write through the Trial Office to the chairman of the TSC, drawing attention to any concerns they may have about the possibility of particular side-effects, or of particular categories of patient requiring special study, or about any other matters thought relevant.

### **10.3. Data Monitoring and Ethics Committee: Monitoring Safety**

If pravastatin for pre-eclampsia demonstrates substantial harm to mother or baby, then this may become apparent before the target recruitment has been reached. Alternatively, new evidence might emerge from other sources that statins show substantial benefit or harm to pregnant women and their babies. To protect against this, during the period of recruitment to the trial, interim analyses of safety and morbidity outcomes will be supplied, in strict confidence, to an independent Data Monitoring and Ethics Committee (DMEC) along with updates on results of other related studies, and any other analyses that the DMEC may request. The DMEC will consider safety every 3 months. The DMEC will also be given reports of data quality

at 6 monthly intervals. As this is a pilot study, there is no intention to stop the study early on the grounds of potential efficacy, and thus the DMEC will not be supplied with unblinded results of the main outcome.

The DMEC will advise the chair of the Trial Steering Committee if, in their view, the trial should be stopped on safety grounds, or if protocol modifications are needed.

## **11. ORGANISATION AND RESPONSIBILITIES**

To ensure the smooth running of the trial and to ensure good clinical practice principles are adhered to, each participating centre should designate individuals who would be chiefly responsible for local co-ordination of clinical and administrative aspects of the trial.

All investigators are responsible for ensuring that any research they undertake follows the agreed protocol, for helping care professionals to ensure that participants receive appropriate care while involved in research, for protecting the integrity and confidentiality of clinical and other records and data generated by the research, and for reporting any failures in these respects, adverse drug reactions and other events or suspected misconduct through the appropriate systems.

### **11.1. Centre eligibility**

Participating centres will be large teaching hospitals, with at least 4500 deliveries per year and day assessment units where suspected pre-eclampsia cases are diagnosed.

### **11.2. Local Co-ordinator at each centre**

Each Centre should nominate a **Consultant Obstetrician** to act as the local Principal Investigator and bear responsibility for the conduct of research at their centre. Close collaboration between all clinical teams is particularly important in pre-eclampsia in order that patients for whom the StAmP Trial is an option can be identified sufficiently early for entry. The responsibilities of the local Principal Investigator will be to ensure that all medical and midwifery staff involved in the care of women with pre-eclampsia are well informed about the trial and trained in trial procedures, including obtaining informed consent. The local PI should liaise with the Trial Coordinator on logistic and administrative matters connected with the trial.

### **11.3. Midwifery Co-ordinator at each centre**

Each participating centre will receive support from a Research Midwife. However, it is also important to identify one Trust midwife as local Midwifery Coordinator with whom the Research Midwife will liaise. The Midwifery Coordinator would be responsible for ensuring that all eligible patients are considered for the trial, that patients are provided with trial information sheets, and have an opportunity to discuss the trial if required. The midwifery coordinator may be responsible for collecting the baseline patient data and for administering the follow-up evaluations. Again, this person would be sent updates and newsletters, and would be invited to training and progress meetings.

### **11.4. The StAmP Trial Office**

The Trial Office at the BCTU is responsible for providing the following trial materials:

- the Site File, containing all documentation required under good clinical practice to define the involvement of the centre in the trial
- an Investigators' folder containing printed materials such as participant information sheets and consent forms, algorithms and pharmacy logs.
- A online randomisation system, including individual log-in and passwords and guidance

These will be supplied to each collaborating centre, after relevant authorisations have been obtained. Additional supplies of any printed material can be obtained on request. The Trial Office also provides the

central randomisation service and is responsible for collection and checking of data (including managing any reports of serious adverse events thought to be due to trial treatment), for reporting of serious and unexpected adverse events to the sponsor and regulatory authorities on behalf of the Chief Investigator and for analyses. The Trial Office will help resolve any local problems that may be encountered in trial participation.

### **11.5. Research Governance**

The conduct of the trial will be according to the Medicines for Human Use (Clinical Trials) Regulations 2004 and any subsequent amendments and the principles of the International Committee on Harmonisation Good Clinical Practice Guidelines.

All centres will be required to sign a Clinical Study Site Agreement and Investigator's Agreement, detailing their commitment to accrual, compliance, Good Clinical Practice, confidentiality and publication. Deviations from the agreement will be monitored and the TSC will decide whether any action needs to be taken, e.g. withdrawal of funding, suspension of centre.

The Trial Office will ensure that any University employed Research Midwives, who will interact with participants in a way that has an impact on the quality of their care, hold an NHS honorary research passport.

